**Fig 2 pone.0337999.g002:**
[figure not shown]
Study Flow Chart.

Inclusion/Exclusion Criteria: Criteria determining whether a patient can participate in the study.

Informed Consent: The patient will be asked to give their written informed consent. In case they are unable to provide legal consent, i.e., due to cognitive impairment, an authorized caregiver will be asked to decide about study participation.

Baseline Characteristics: Initial patient data collected at baseline: age, sex, past medical and surgical history according to standard of care.

Charlson Comorbidity Index (CCI) (documented at baseline): A method to collate comorbidities of patients into a score that categorizes their overall severity. Each condition is assigned a score of 1, 2, 3 or 6, depending on the risk of dying associated with each one. Additionally, age is incorporated as a risk factor: patients receive 1 additional point for each decade over 50 years of age (i.e., 50–59 years = +1, 60–69 = +2, 70–79 = +3, ≥ 80 = +4).

### 
Recruitment status

Enrolment is anticipated to begin in the 3^rd^ quarter of 2025. We estimate recruitment completion (last patient in) by late 2027, given the enrolment target of 322 and the number of sites. The 6-month follow-up of the last patient should be completed by mid-2028. Thus, we expect the primary analysis to commence in Q3 2028, with results reported in late 2028. These timelines may be adjusted depending on actual recruitment rates.

Neurological Exam: Assessment of the patient’s neurological status to screen for neurological deficits caused by spinal cord injury from the odontoid fracture or other pathologies, according to standard of care.

Randomization: Patients will be randomized to either the conservative or surgical group according to a predefined process.

CT Cervical Spine: A computed tomography (CT) of the cervical spine will be obtained at the baseline visit to determine the fracture type and its dislocation measured in mm, and at Visits 3 to check for the presence of fracture healing (both groups), secondary dislocation in mm (both groups) and integrity of the implant material (surgical group).

Barthel Index (BI): A scale to measure performance in activities of daily living that constitutes the primary outcome in the statistical analysis after 12 weeks.

EuroQol-5D Questionnaire (EQ-5D): A standardized instrument to measure health outcomes, used within secondary analyses to compare the quality of life between groups.

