### Sample size calculation

Assuming a non-inferiority study design with a one-sided α = 0.025, we set the expected difference in change of BI scores between the two groups to 0. Unnanuntana et al. (2018) show that the minimal clinically important difference (MCID) of the BI in elderly patients after a surgical intervention is 9.8 [48]. Bouwstra et al. (2018), conclude the smallest detectable change in BI in a geriatric nursing home population to be 3.0 [32]. It is common practice to choose a non-inferiority margin for a patient-reported outcome such as the BI, which is lower than the MCID, see Copay et al [49]. Thus, we set the non-inferiority margin to 5, which is closer to the smallest detectable change than to the MCID and therefore more conservative. The standard deviation of the difference in BI between baseline and week 12 was estimated at 12.7 referencing prior work by Unnanuntana et al [48]. Based on these assumptions, a sample size of 137 in each group (274 in total) will have 90% power to reject the null hypothesis of the one-sided 2.5% significance level t-test that the surgical group is inferior to the conservative group in favor of the alternative hypothesis that the surgical group is non-inferior to the conservative group. Assuming a drop-out rate of 15%, a total of 322 patients will need to be included (161 per arm).

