### Statistical analyses

Analysis will be performed on all patients who were randomized to the study. The primary estimand and its attributes are described in Table 1.

**Table 1 pone.0337999.t001:** Definition of all five attributes used to construct the primary estimand for the SCORE study (non-inferiority setting).

Primary estimand	
**Population**	Geriatric patients with recent type II & III odontoid fractures (as defined by trial inclusion/exclusion criteria).
**Variable**	Functional status accessed as the change in Barthel Index (BI) between baseline and 12 weeks thereafter
**Treatment**	• Surgical stabilization C1-2 by dorsal screw-rod construct (duration of treatment: Approximately 100 min + approximately 6 days hospital stay) or • Conservative therapy by external cervical collar immobilization (duration of treatment: 12 weeks)
**Population-summary measure**	Mean difference, including 95%CI.
**Intercurrent event (IE) and strategy**	• Refusal of therapy as randomized – multiple imputations (hypothetical estimate) • Crossover from the conservative to the surgical arm after randomization but before week 12 – use the last available BI value before surgery as best estimate of the hypothetical BI value at week 12 *Note: Cross-over from the conservative to the surgical arm after week 12 is allowed, as it does not influence the primary variable, which is measured at week 12* • Loss to follow-up after start of therapy – multiple imputations; missing at random assumed • Death – (expected ca. 10%) multiple imputations (hypothetical estimate)

Intercurrent events (IEs) will be dealt with using a hypothetical strategy to determine the treatment effect without the abovementioned IEs.

The primary endpoint will be tested using a mixed model for repeated measures (MMRM) of BI, where treatment, time, their interaction, baseline BI scores, age, and CCI will be fixed covariates, and study center will be a random covariate. In case the model does not converge due to small centers, the covariate center will be abandoned. The adjusted mean difference between groups in the primary outcome will be tested at the 12-week time point.

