Due to the rising prevalence as well as the clinical and socioeconomical impact of OFs, Level I evidence from a randomized clinical trial regarding optimal treatment would provide a clear clinical utility for any health-care provider world-wide. Both treatment options – immobilization via a cervical collar and surgical stabilization with a screw-rod-system – are established procedures requiring standard materials only. Overall, there is a slight trend in favour of surgical therapy based on expert opinions and retrospective studies [14]. However, no large multi-center study has yet been carried out that compares conservative and surgical therapy of geriatric OFs randomized. There are two yet unpublished clinical trials: INNOVATE and USOFT, which are enlisted within trial registries [24,26]. These trials however put emphasis on a different scientific hypothesis; the main focus of the planned clinical study lies in the quality of life and functional autonomy of elderly patients, which should represent the prime outcome benchmark for a specialist treating this population. Geriatric patients are especially vulnerable to acute injuries that may kickstart a cascade of further severe comorbidities [7,21,52]. By optimizing and standardizing the therapy of OFs, a number of serious consequences can be prevented [15,53,54]. In the same vein, clinical dementia rates in the elderly population reach up to 15%, which entails dependency on nursing homes [14]. This confounds the success rate of the conservative treatment, causing its failure in 50–60% due to non-compliance in wearing the collar without supportive nursing care [17]. We deliberately designed both the inclusion and exclusion criteria to mirror real-life practice, including patients with dementia specifically because of their expected non-compliance and associated complications prominent in this subpopulation. Thus, we aim to provide high-class evidence that is transferrable to clinical practice and guideline recommendations.

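### The primary model has no term for dementia, which the protocol itself names as a driver of collar failure; pre-specifying one is a cheap safeguard for the missing-at-random analysis

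*Protocol article*

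**What the plan says.** **Primary model** (Statistical analyses). The 12-week comparison comes from a mixed model for repeated measures with treatment, time and their interaction. On the other terms the text reads "baseline BI scores, age, and CCI will be fixed covariates, and study center will be a random covariate". There is no dementia or cognition term. The CCI is described under Data to be collected as one score that adds up comorbidities and age. Randomization is stratified by center only.

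**Removed or missing values** (Table 1). BI after refusal of the allocated therapy, loss to follow-up or death is handled by multiple imputation, with missing at random stated for loss to follow-up. Crossover to surgery before week 12 is handled differently: the last BI before surgery is used. Poor collar adherence is not listed as an intercurrent event.

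**Dementia** (Discussion, Rationale). The article puts dementia at up to 15% and says it undermines conservative treatment, "causing its failure in 50–60% due to non-compliance in wearing the collar without supportive nursing care". It describes the eligibility criteria as "including patients with dementia specifically because of their expected non-compliance and associated complications prominent in this subpopulation".

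**Baseline data** (Data to be collected). The items include "past medical and surgical history according to standard of care".

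**Sensitivity analysis** (end of the statistical text). Patients with and without 3-month data are compared. Variables associated with missingness are then added to the mixed model as a further sensitivity analysis.

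**The concern.** Missing at random is a statement conditional on the variables in the model. A factor that predicts both who loses the week-12 value and what that value would have been has to be in the model, or the estimate drifts towards the patients who remain. The article names such a candidate and leaves it out of an otherwise explicit covariate list. A summed score cannot tell dementia from any other condition that carries the same points.

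If demented patients recover less BI and are removed more often from one arm, the mean of that arm is too high. More removal in the collar arm shifts the difference against surgery, and a true non-inferiority may be missed. More removal in the surgical arm shifts it in favour of surgery, and the chance of wrongly declaring non-inferiority rises. The 5-point margin leaves little room for either.

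**Working it through.** **Inputs from the protocol article**
- Sample size calculation: one-sided alpha 0.025; true difference between arms taken as 0; 137 evaluable per group; 161 randomized per arm.
- Margin, same section: "we set the non-inferiority margin to 5".
- Variability, taken there from an outside study: "The standard deviation of the difference in BI between baseline and week 12 was estimated at 12.7".
- Discussion: dementia up to 15%. Table 1: deaths about 10%.

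**Assumptions not in the article**
- Dementia lowers BI change by 8 points beyond baseline BI, age and CCI (range 5 to 12).
- Apart from deaths, which are taken as equal in both arms and unrelated to dementia, 5% of patients are removed. The exception is demented collar patients, of whom 20% or 35% are removed.

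**Step 1. The plan's own figure.** The standard error is 12.7 × √(2/137) = 1.534. The noncentral t distribution with 272 degrees of freedom and noncentrality 5/1.534 gives power 90.1%. The stated 137 per group is reproduced.

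**Step 2. Bias.** With collar-arm removal q among demented patients, their share of the observed collar patients is 0.15(1 − q) / [0.15(1 − q) + 0.85 × 0.95]. The bias is 8 × (0.15 − share). The surgical arm contributes none, because removal there is 5% in both subgroups.
- q = 20%: share = 0.1200/0.9275 = 0.129; bias = 8 × 0.0206 = 0.17 points.
- q = 35%: share = 0.0975/0.9050 = 0.108; bias = 8 × 0.0423 = 0.34 points.

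**Step 3. Power.** Replace the margin of 5 by 5 minus the bias, with SD 12.7 and 137 per arm.
- q = 20%: 88.1%.
- q = 35%: 85.7%.

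A simulation with 4000 trials per setting, in which the CCI carries part of the dementia effect, gives biases of 0.18 and 0.33 points and power of 87.9% and 85.5%. With a dementia term the bias is about 0 and power about 91%.

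**Step 4. Other effect sizes, same formula.**

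| Dementia effect | q = 20%: bias, power | q = 35%: bias, power |
|---|---|---|
| 5 points | 0.10, 88.9% | 0.21, 87.5% |
| 8 points | 0.17, 88.1% | 0.34, 85.7% |
| 12 points | 0.25, 87.0% | 0.51, 83.1% |

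**Step 5. Other patterns of removal, 8-point effect.**
- Equal removal in both arms: the two shares are equal, the bias is 0 and power is 90.1%.
- 20% in the collar arm against 10% in the surgical arm: the surgical share is 0.1350/0.9425 = 0.143, so the net bias is 8 × (0.1432 − 0.1294) = 0.11 points.
- Pattern reversed (35% surgical, 5% collar): 0.34 points in favour of surgery. One-sided error at the margin rises from 2.5% to about 4.1% by formula and about 3.9% by simulation.

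**Step 6. Precision.** The sample size comes from an unadjusted t-test, so leaving the term out does not itself lower the planned power. If the SD of 12.7 already contains the dementia variance, adjustment reduces it to √(12.7² − 0.15 × 0.85 × gap²). For gaps of 5 and 10 points this is 12.57 and 12.19, and power at 137 per arm is 90.7% and 92.3%.

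**The case against.** The strongest reply is that the article does not establish the link between dementia and imputation. A reader might take the 50–60% collar failure as the share of demented collar patients whose BI would be imputed. The article does not support that. The figure concerns adherence without nursing support. Non-adherence is not an intercurrent event in Table 1, so the observed BI stays in, and failure that leads to surgery is a crossover, handled by the last value. Only refusal, loss to follow-up and death are imputed. This stands, and it is why the working stops at 35%.

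A reader might also infer that the effect acts in the collar arm only and always costs power. That is not shown either. Refusal can occur in both arms, and Step 5 shows that existence and sign depend on the difference between arms.

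Third, the article does not list the imputation variables. One cannot say that values are filled in from mostly non-demented patients, and a full plan may already include dementia there. This stands too. It does not alter the stated covariate list of the primary model.

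Fourth, the 8-point effect is assumed, and the CCI may absorb part of dementia. At 20% removal the bias is 0.17 points against a margin of 5, in the conservative direction. This is a fair description of the size.

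Fifth, the sensitivity analysis could bring dementia in. It covers the issue only in part: its covariates are chosen after missingness has been seen, and it lies outside the confirmatory test.

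**Conclusion.** The point holds as a cheap improvement, not as a demonstrated bias. The article identifies dementia as a driver of collar failure and enrols these patients deliberately, yet fixes a primary model without a dementia term. The harm is conditional on two things it does not quantify: an effect of dementia on BI change beyond baseline BI, age and CCI, and a difference between arms in refusal or loss among demented patients.

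With 15% dementia, an 8-point effect and 20–35% against 5% removal, the bias is about 0.2–0.3 points against surgery and power is about 86–88%. With equal removal nothing is lost. With the reverse pattern, one-sided error rises to about 4% at 35% against 5%. Since the direction cannot be known in advance, a pre-specified term is better than reliance on a favourable pattern.

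**What to change.** - Add baseline dementia or cognitive impairment (yes/no) as a fixed covariate in the primary mixed model, specified before outcome data are compared by arm.
- Name the same variable in the imputation model for refusal and loss to follow-up.
- Take it from the medical history, with one eCRF tick box so that all sites record it alike. The article mentions history only in general terms, so it should not be assumed that the item is already captured uniformly.
- Treat an interaction with arm in the imputation model as optional. Of about 161 × 0.15 = 24 demented patients per arm, only about 24.15 × 0.90 × 0.65 = 14 to 24.15 × 0.90 × 0.80 = 17 would be observed in the collar arm under the assumptions above, which is thin support for an interaction.

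The cost is one degree of freedom and possibly one eCRF item. The sample size, visits and treatments stay as they are. The term removes this bias only so far as dementia is the omitted driver, so the existing sensitivity analysis on missing data should be kept.

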### Randomization

After giving informed consent, patients are randomized to study arms during the baseline visit using randomizer.at, an online-randomization tool. Randomizer.at uses pre-defined randomization algorithms which are tailored to our study needs. Allocation occurs on demand in a 1:1 ratio, stratified by study center using permuted blocks. Assignment to the study arm is concealed and only revealed at the time of randomization through the password-protected, secure website.

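### The convergence fallback drops centre, the only stated stratification factor, from the primary model; if centres differ, the confidence interval becomes slightly too wide

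*Protocol article*

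**What the plan says.** The Randomization section of the protocol article states: "Allocation occurs on demand in a 1:1 ratio, stratified by study center using permuted blocks". No other stratification factor is named.

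Under Statistical analyses, the test of the primary endpoint is set out: "The primary endpoint will be tested using a mixed model for repeated measures (MMRM) of BI". Treatment, time, their interaction, baseline Barthel Index (BI), age and the Charlson index are fixed terms, and "study center will be a random covariate". The treatment difference is tested at week 12. The same paragraph gives the fallback: "In case the model does not converge due to small centers, the covariate center will be abandoned". No step is placed between the full model and the model without centre.

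**The concern.** Blocked allocation within centre makes the two arms nearly equal in size at each site. Differences between sites then largely cancel out of the treatment comparison, and its true sampling error is smaller than under unstratified allocation. A model without centre does not know this. It puts the between-centre variance into the residual and reports a standard error that is too large.

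The rule is also broader than its cause. A few small sites may prevent convergence, yet centre is removed for the large sites as well.

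Non-inferiority is decided on a confidence limit set against a margin of 5 BI points. If the limit lies further out than it should, the trial can miss a non-inferiority that its data support. The questions are how large this effect is and in which direction it acts.

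**Working it through.** **Inputs from the Sample size calculation section.** Margin 5 ("we set the non-inferiority margin to 5"); expected difference 0; SD of the change 12.7 ("The standard deviation of the difference in BI between baseline and week 12 was estimated at 12.7"); one-sided α 0.025; 137 evaluable patients per arm; 15% drop-out; 322 in total.

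**Inputs that the documents do not give, hence assumptions.** Centre ICC, number and relative size of centres, and block size.

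**Step 1: the plan's own figure.** Normal approximation: n = 2 × (1.960 + 1.282)² × 12.7² / 5² = 135.6, so 136 per arm. The noncentral t gives 137 per arm with power 0.901. Drop-out: 274 / 0.85 = 322.4, which rounds up to 323 against 322 stated, a rounding difference. The sample size reproduces, and it contains no centre term.

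**Step 2: analytic effect of dropping centre.** Hold the total SD at 12.7 and suppose perfect balance within every centre.
- Reported SE without centre: 12.7 × √(2/137) = 1.534.
- True SE: 1.534 × √(1 − ICC).
- Overstatement: 1/√(1 − ICC).
- Actual one-sided error: 1 − Φ(1.960/√(1 − ICC)).
- Power without centre: Φ((5 − 1.960 × 1.534) / true SE).
- Power with centre kept: Φ(5 / true SE − 1.960).

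| Assumed ICC | True SE | SE too large by | One-sided error | Power without centre | Power with centre |
|---|---|---|---|---|---|
| 0 | 1.534 | 0% | 0.0250 | 0.903 | 0.903 |
| 0.02 | 1.519 | 1.0% | 0.0239 | 0.905 | 0.909 |
| 0.05 | 1.496 | 2.6% | 0.0222 | 0.909 | 0.917 |
| 0.10 | 1.456 | 5.4% | 0.0194 | 0.915 | 0.930 |
| 0.20 | 1.372 | 11.8% | 0.0142 | 0.927 | 0.954 |

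These overstatements are upper bounds, because incomplete blocks and drop-out prevent perfect balance within centres.

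**Step 3: simulation with imperfect balance.** 322 patients, blocks of 4, 15% random drop-out, unequal centres, one time point, centre omitted against centre as a fixed effect; 10,000 runs for error and 4,000 for power.

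| Centres | Assumed ICC | Reported / empirical SE without centre | One-sided error without centre | Power without / with centre |
|---|---|---|---|---|
| 10 | 0.05 | 1.529 / 1.515 = 1.009 | 0.0251 | 0.907 / 0.912 |
| 20 | 0.05 | 1.530 / 1.497 = 1.022 | 0.0218 | 0.910 / 0.917 |
| 10 | 0.10 | 1.525 / 1.486 = 1.026 | 0.0245 | 0.910 / 0.924 |
| 20 | 0.10 | 1.527 / 1.474 = 1.036 | 0.0198 | 0.912 / 0.927 |
| 20 | 0.20 | 1.521 / 1.398 = 1.088 | 0.0178 | 0.928 / 0.955 |

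The Monte Carlo error on a 2.5% rate is √(0.025 × 0.975 / 10,000) = 0.0016, so single error rates should not be over-read. The direction agrees with Step 2 and the size is smaller. At ICC 0.02 the difference is within simulation error.

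**Step 4: does keeping centre cost anything?** With 30 unequal centres and an unpooled fixed effect, power was 0.887 against 0.897 without centre at ICC 0, 0.903 against 0.905 at ICC 0.05, and 0.918 against 0.909 at ICC 0.10. So many unpooled small centres can cost about one point. When centres with fewer than 6 patients are pooled, the fixed effect restores calibration over 10 to 30 centres. It gains roughly 0.3 to 1.4 points at ICC 0.05 to 0.10 and costs at most about 0.2 points at ICC 0.

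**The case against.** The case for leaving the rule alone is substantial.

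- **The error is on the safe side.** A reader might infer that an analysis ignoring the stratification puts the non-inferiority claim at risk. It does not: the interval is too wide, not too narrow. This stands.
- **No planned power is lost.** A reader might infer that the fallback leaves the trial underpowered. The 90% was computed from a two-group t-test without centre, and in Step 2 power without centre is above 0.90 at every ICC. What is lost is a gain that the plan never claimed. This stands.
- **The trigger may select the harmless case.** Non-convergence often goes with centre variance near zero, and then dropping centre changes almost nothing. The relevant ICC is also the residual one after baseline BI, age and the Charlson index. Both points stand and make the figures above cautious.
- **The rule is pre-specified, and any replacement also depends on how the fit behaves.** This stands too, so dependence on the fit is not a reason to change it.
- **Centre should not be kept at any price.** Step 4 shows a cost if many small centres are left unpooled, so the documents give no ground for saying that centre must never be dropped.
- **Detailed fallback orders belong in the analysis plan, which is not shown.** This does not settle the matter. The article does not leave the fallback open; it fixes one, and the point concerns that stated rule.

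**Conclusion.** The point holds as a minor one. The stated fallback omits the only named stratification factor for all sites when small ones prevent convergence, although alternatives that respect the design better cost almost nothing.

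If centres differ and the fallback is used, the standard error is overstated by up to about 2-3% at an assumed ICC of 0.05 and about 3-5% at 0.10. One-sided error tends to lie somewhat below 2.5%, and about 0.3 to 1.5 power points are lost relative to keeping centre. There is no effect if residual centre variance is near zero.

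The sizes rest on assumed ICC, number of centres and block size, and on a single-time-point analysis standing in for the repeated-measures model. The direction, conservative when centres differ, follows from the stratified allocation itself.

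**What to change.** Replace the fallback sentence with a fixed order that keeps centre as long as possible, for example:

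> If the model does not converge, centres below a size fixed before any outcome comparison are pooled and the model is refitted. If it still does not converge, pooled centre is fitted as a fixed effect. Centre is omitted only as the last step. The same step is applied to all imputed datasets.

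The size threshold is the trial team's choice; the check above used fewer than 6 patients. Because the trial is open-label, it should be set without sight of outcomes by arm. The last clause matters because intercurrent events and missing values are multiply imputed, and the model could converge in some imputed datasets and not in others.

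The cost is a short amendment and no extra data. The statistical price is a few degrees of freedom, at most about 0.2 power points when centres do not differ and small ones are pooled. The article expects the primary analysis in the third quarter of 2028, so on that timeline the change can be made beforehand.
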